## 1 INTRODUCTION

In order to determine what drives liver disease progression in HIV-HBV co-infected patients, a group of 67 patients on suppressive HBV-active HAART were prospectively followed and changes in liver disease progression were measured over 3 years, with study visits every 6 months (baseline, 6, 12, 18, 24, 30, and 36 months of follow-up) [1, 2]. The schedule of assessments is listed in Appendix 1. Liver fibrosis (assessed by transient elastography) and peripheral blood mononuclear cells (PBMCs) were assessed at baseline then annually.

**Table 1 Participant recruitment by clinical site and overall**

| Site                                  | Provided informed consent & follow-up post baseline visit | Follow-up at 3 years |
|---------------------------------------|-----------------------------------------------------------|----------------------|
| HIV-NAT, Bangkok                      | 31/67 (46.3%)                                             | 30/58 (51.7%)        |
| Australia:                            | 36/67 (53.7%)                                             | 24/58 (41.3%)        |
| The Alfred - Melbourne                | 20/67 (31.3%)                                             | 14/58 (24.1%)        |
| Melbourne Sexual Health Centre (MSHC) | 10/67 (14.9%)                                             | 8/58 (13.8%)         |
| St Vincent – Sydney (SVH)             | 6/67 ( 9.0%)                                              | 6/58 (10.3%)         |
| Overall                               | 67 ( 100%)                                                | 58/67 (86.6%)        |

## 2 DATA SOURCE

Data was collected using paper case report forms (CRFs), peripheral blood mononuclear cells (PBMC), plasma samples and Fibroscans (transient elastography). CRF data was entered into an Access database. Once all data was entered into Access, it was exported to Excel, checked and cleaned. Data clarifications were sent to sites as necessary, and any changes to the database resulting from clarification were logged in an electronic file. Samples collected were analysed at the [name]/[name] Laboratory, Doherty for markers of immune activation and microbial translocation. All data was de-identified and kept securely at the Doherty Institute on password-protected computers, files are backed-up and maintained by University of Melbourne IT.

## 3 ANALYSIS OBJECTIVES

### 3.1 Aim 1

To determine if changes in microbial translocation or inflammation can predict liver disease progression in HIV-HBV infected individuals receiving HBV-active HAART. We hypothesise that microbial translocation and markers of immune activation are associated with liver disease severity and liver disease progression in HIV-HBV co-infection.

### 3.1 Aim 2

To explore whether any of the key subgroups differ in fibrosis progression. More details on the defined subgroups of interest can be found in Section 4.

## 4 ANALYSIS SETS/ POPULATIONS/SUBGROUPS

The analysis set consists of all 67 participants across all sites. Liver disease progression as measured using Fibroscan is defined as an increase in Fibroscan Stage (F1≤5.8 kPa (kiloPascals), F2 5.9-7.5 kPa, F3 7.6-9.3 kPa, F4>9.4 kPa) from baseline result to last study time point (either 36 months or last completed data point). These patients are referred to as “**progressors**”. Patients in the study are expected to show either no change, regression (decrease in Fibroscan Stage), or progression. Patients who do not show progression are referred to as “**non-progressors**”. Some participants’ fibrosis stage may fluctuate between first and last Fibroscan, such cases will be described but status will be defined only on first and last Fibroscan result. In addition, a pre-determined secondary definition of fibrosis progression was added, defined as 20% increase and ≥2 kPa (at least one value >5.9 kPa) [3].

Key subgroups of interest based on study entry characteristics include:

- HBeAg status at baseline (positive vs negative)
- Nadir CD4 cell count at baseline (>200 vs ≤200)
- CD4 nadir (%) (<10 or ≥10%)
- HIV viral load at CD4 nadir at baseline (>200,000 vs ≤ 200,000)
- ART duration (≤10 or >10 years)
- Derangement of ALT from normal range (yes vs no) – cut-offs are gender and site specific

Other exploratory subgroups (depending on numbers in each subgroup): gender (male vs female) and site (Bangkok vs others).

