## 5 ENDPOINTS AND COVARIATES

**Table 2 Endpoints and covariates**

| Grouping                                                                                        | Variable                                                                                              | Comment                                                                          |
|-------------------------------------------------------------------------------------------------|-------------------------------------------------------------------------------------------------------|----------------------------------------------------------------------------------|
| Endpoints (measured repeatedly over time)                                                |                                                                                                       |                                                                                  |
| Microbial translocation/
immune activation
Collected 6-monthly (7)
analysed yearly (4) | sCD14 (pg/mL)
CXCL10 (pg/mL)                                                                       | Continuous
Continuous                                                         |
| Hepatic Inflammation
Collected 6-monthly (7)
analysed yearly (4)                          | ALT (IU/L)
AST (IU/L)
Albumin (g/L)                                                             | Continuous
Continuous
Continuous                                           |
| Liver disease severity
Collected yearly (4)                                                  | Fibrosis (kPa)                                                                                        | Continuous                                                                       |
| Liver disease progression
One value (1)                                                      | Progression (Grade change) (yes/no) (primary)
Progression (kPa change) (yes/no) (secondary)        | Binary
Binary                                                                 |
| Markers of cell death
Collected 6-monthly (7)
analysed yearly (4)                         | HMGB1 (ng/mL)                                                                                         | Continuous                                                                       |

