| Treatment                                               | HBV-active agents (<2/2)                                                                                                                                                                                                                                    | Binary                                                                                 |
| Liver fibrosis                                          | Fibroscan stage (1/2/3/4)
Fibroscan score ( $\leq$ F2, >F2)                                                                                                                                                                                              | Categorical
Binary                                                                  |

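### The primary grade-change rule cannot register progression in participants who start at F4 but counts them as non-progressors, and a reading of 9.4 kPa has no stage

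*SAP*

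**What the plan says.** Section 4 of the SAP sets the rule: "Liver disease progression as measured using Fibroscan is defined as an increase in Fibroscan Stage", with stages and interval given as "F1≤5.8 kPa (kiloPascals), F2 5.9-7.5 kPa, F3 7.6-9.3 kPa, F4>9.4 kPa) from baseline result to last study time point". Fluctuation between scans is described but ignored for classification: "status will be defined only on first and last Fibroscan result". The remainder form the comparison group: "Patients who do not show progression are referred to as" non-progressors. Nobody is left out, since "The analysis set consists of all 67 participants across all sites".

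Table 2 (Section 5) lists the endpoint as "Progression (Grade change) (yes/no) (primary"). It also lists the study-entry covariate "Fibroscan stage (1/2/3/4"), so participants at stage 4 on entry are foreseen. A two-level version, at most F2 against above F2, is listed as well. No rule says how a participant at F4 on entry is to be handled.

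Section 4 adds a secondary definition, "defined as 20% increase and ≥2 kPa (at least one value >5.9 kPa"), and Section 7.1.1 plans mixed models of kPa as a continuous outcome. Section 8 plans no sensitivity analyses.

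**The concern.** A binary outcome should be attainable by everyone in its denominator. Here it is not: a participant at F4 at baseline has zero probability of the primary event by definition, yet joins the comparison group whatever the later scan shows. The non-progressors then mix people whose fibrosis did not advance with people whose advance cannot be recorded, and the latter have the highest stiffness at entry.

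The label is used widely. It decides the baseline tests in Section 7.1, is the outcome of logistic model 1, is the grouping in the kPa trajectory comparison in Section 7.1.1, and defines outputs 3A1 to 3C2 in Section 11. Section 3.1 hypothesises that the markers are associated with both severity and progression. If markers are higher in severe disease, baseline-F4 participants raise the non-progressor marker level and pull the marker-progression association toward, or below, the null.

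Separately, F3 stops at 9.3 kPa and F4 begins above 9.4 kPa. A first or last reading of 9.4 kPa leaves the participant's stage undefined.

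**Working it through.** The SAP gives no figure to reproduce here; the check is of the classification rule.

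**Coverage of the stages.** Coding the four bands as written and stepping from 2.0 to 75.0 kPa in 0.1 kPa steps (range and step are assumptions; the step matches the one-decimal cut-offs) leaves one value without a stage, 9.4 kPa. No value falls in two stages. Changes such as 9.3 to 9.4 or 9.4 to 9.5 cannot be classified.

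**Ceiling.** Among all pairs with a baseline of 9.5 to 75.0 kPa, none gives a stage increase. The two definitions compare as follows:

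| First to last (kPa) | Primary (stage) | Secondary (at least 20% and at least 2 kPa, one value above 5.9) |
|---|---|---|
| 5.8 to 5.9 | F1 to F2: progressor | rise 0.1 kPa: no |
| 9.5 to 11.5 | F4 to F4: non-progressor | rise 2.0 kPa, 21%: yes |
| 10 to 40 | F4 to F4: non-progressor | rise 30 kPa, 300%: yes |

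**Entry stage as a predictor in model 1.** Section 7.1.1 relates the Table 2 covariates to each endpoint. At entry stage 4 the event count is 0 by construction, so that level has no finite log odds ratio. For the two-level covariate, let n3 and n4 be the numbers at F3 and F4 on entry and p3 the event probability at F3. The event probability above F2 is p3 × n3/(n3 + n4), which is below p3 whenever n4 > 0. The odds ratio for above F2 is lowered by definition alone.

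**Effect on the denominator.** The baseline-F4 count is not in the SAP. Assumed shares of 5%, 10% and 20% of 67 give 3, 7 and 13 participants, leaving 64, 60 and 54 at risk. Borrowing the 8% from Section 9 as the rate among those at risk:

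- 0.08 × 64 = 5.1 events, or 5.1/67 = 7.6% in the full set
- 0.08 × 60 = 4.8 events, or 7.2%
- 0.08 × 54 = 4.3 events, or 6.4%

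**Illustrative dilution of a marker difference.** Assume 5 progressors (0.08 × 67 = 5.4, rounded down) and 67 − 5 = 62 non-progressors, of whom k were at F4 at baseline with marker levels d SD higher, and a true difference of 0.5 SD. The non-progressor mean rises by (k/62) × d, and the share of the difference lost is that divided by 0.5:

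| k | d = 0.4 SD | d = 0.8 SD |
|---|---|---|
| 3 | 0.019 SD, 4% | 0.039 SD, 8% |
| 7 | 0.045 SD, 9% | 0.090 SD, 18% |
| 13 | 0.084 SD, 17% | 0.168 SD, 34% |

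The values of k, d and 0.5 SD are all assumptions.

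**The case against.** The best defence is that the plan does not depend on the grade-change endpoint alone. The secondary definition and the continuous kPa outcome models have no ceiling, and a rise from 10 to 40 kPa would show in both. That stands, and it limits the damage. It does not repair the primary endpoint, and the trajectory comparison that groups participants by progressor status inherits the faulty label.

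A reader might infer that the planned regressions of progression on the inflammatory markers are biased. The SAP does not support that: Table 2 lists sCD14, CXCL10, HMGB1 and the other soluble mediators as endpoints, not as covariates for model 1. Formal exposure of the marker comparison runs mainly through the baseline rank-sum tests, which do not test the mean shift computed above; the follow-up marker outputs by status are summaries and plots.

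A reader might also infer that entry stage makes model 1 as a whole uninterpretable. Separation is forced only at the F4 level of one covariate. The stated adjustment is for entry CD4+ T-cells, and the two-level coding includes F3 participants, who can progress.

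On size, with 5 against 62 the standard error of a mean difference is √(1/5 + 1/62) = 0.46 SD, so the illustrated shifts of 0.02 to 0.17 SD are small beside sampling error. That is fair, but imprecision does not excuse a systematic misclassification, and Section 7.2 asks readers to weigh magnitude and direction.

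The 9.4 kPa gap looks like a slip in an inequality and alone would be minor.

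**Conclusion.** The primary definition is wrong as written and should be fixed. Two facts follow from Section 4 without any assumption: a participant at F4 at baseline cannot be a primary progressor and is counted as a non-progressor, and 9.4 kPa has no stage. The consequences reach the primary binary endpoint, the baseline tests, model 1, the kPa trajectory comparison and the outputs by progressor status.

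The size and direction of any resulting bias cannot be determined from the SAP, because the baseline-F4 count is not given. The 4% to 34% range is an illustration, and its direction holds only if markers are higher in severe disease. It would be too strong to say that a definite share of the marker signal is lost, or that the study's findings on liver stiffness are invalid: the former rests on values the SAP does not contain, and the latter ignores the two kPa-based outcomes that have no ceiling.

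**What to change.** 1. Report the number of participants at F4 at baseline.
2. Run the grade-change analysis in participants at F1 to F3 at baseline and show it beside the all-67 result. Section 13 reports fitted models and changes made once data were available, so label the analysis as a late change if data have been seen.
3. Describe baseline-F4 participants separately with the existing kPa-based secondary definition.
4. Do not interpret an odds ratio for entry stage 4 in model 1. State beside any result for above F2 that its F4 members could not have the event.
5. Have the sponsor reconcile the F3 and F4 bands so that 9.4 kPa falls in exactly one stage. The SAP does not show which was intended.

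The cost is SAP wording and re-tabulation of data already collected. The at-risk analysis has a smaller denominator (64 to 54 under the assumed 3 to 13), but it loses no primary events, because the participants left out could not have one.

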## 5 ENDPOINTS AND COVARIATES

**Table 2 Endpoints and covariates**

| Grouping                                                                                        | Variable                                                                                              | Comment                                                                          |
|-------------------------------------------------------------------------------------------------|-------------------------------------------------------------------------------------------------------|----------------------------------------------------------------------------------|
| Endpoints (measured repeatedly over time)                                                |                                                                                                       |                                                                                  |
| Microbial translocation/
immune activation
Collected 6-monthly (7)
analysed yearly (4) | sCD14 (pg/mL)
CXCL10 (pg/mL)                                                                       | Continuous
Continuous                                                         |
| Hepatic Inflammation
Collected 6-monthly (7)
analysed yearly (4)                          | ALT (IU/L)
AST (IU/L)
Albumin (g/L)                                                             | Continuous
Continuous
Continuous                                           |
| Liver disease severity
Collected yearly (4)                                                  | Fibrosis (kPa)                                                                                        | Continuous                                                                       |
| Liver disease progression
One value (1)                                                      | Progression (Grade change) (yes/no) (primary)
Progression (kPa change) (yes/no) (secondary)        | Binary
Binary                                                                 |
| Markers of cell death
Collected 6-monthly (7)
analysed yearly (4)                         | HMGB1 (ng/mL)                                                                                         | Continuous                                                                       |
| Immune mediators
Collected 6-monthly (7)
analysed yearly (4)                              | TNF-α (pg/mL)
IL-10 (pg/mL)
IL-18 (pg/mL)
CXCL-9 (pg/mL)
CXCL-11 (pg/mL)
CCL-2 (pg/mL) | Continuous
Continuous
Continuous
Continuous
Continuous
Continuous |

| Grouping                                                | Variable                                                                                                                                                                                                                                                    | Comment                                                                                |
|---------------------------------------------------------|-------------------------------------------------------------------------------------------------------------------------------------------------------------------------------------------------------------------------------------------------------------|----------------------------------------------------------------------------------------|
|                                                         | CCL-3 (pg/mL)
CCL-4 (pg/mL)
CCL-5 (pg/mL)                                                                                                                                                                                                             | Continuous
Continuous
Continuous                                                 |
| CD4+
CD8+                                            | CD4+ T-cell count (cells/ $\mu$ L)
CD4+ T-cells (%)
CD8+ T-cell count (cells/ $\mu$ L)
CD8+ T-cells (%)
CD4:CD8 ratio                                                                                                                           | Continuous
Continuous
Continuous
Continuous
Continuous                     |
| Covariates (measured once at study entry) |                                                                                                                                                                                                                                                             |                                                                                        |
| Demographics                                            | Gender (male/female*)
(* TransGender Female categorised as Female)
Age (years)
Body Mass Index (kg/m  )
Site/Country                                                                                                                | Binary

Continuous
Continuous
Binary                                       |
| Adherence and alcohol questionnaires                    | Alcohol excess intake (yes/no)                                                                                                                                                                                                                              | Binary                                                                                 |
| CD4 nadir
CD4+
CD8+                               | Nadir CD4 cell count (cells/ $\mu$ L)
Nadir CD4 cell count (>200/ $\leq$ 200 cells/ $\mu$ L)
Nadir CD4 cells (%)
Nadir CD4 cells (<10/ $\geq$ 10%)
CD4+ T-cell count (cells/ $\mu$ L)
CD4+ T-cells (%)
CD8+ T-cell count (cells/ $\mu$ L) | Continuous
Binary
Continuous
Binary
Continuous
Continuous
Continuous |
| HIV RNA at time of CD4 nadir                            | HIV viral load at CD4 nadir (cps/mL)
HIV viral load at CD4 nadir (>200,000/ $\leq$ 200,000 cps/mL)                                                                                                                                                       | Continuous
Binary                                                                   |
| Hepatitis serology                                      | HBeAg status (positive/negative)
ALT (IU/mL)
ALT derangement from normal range (yes/no)                                                                                                                                                               | Binary
Continuous
Binary                                                         |
| HIV characteristics                                     | Duration of ART (>10/ $\leq$ 10 years)
Time on ART (years)                                                                                                                                                                                               | Binary
Continuous                                                                   |
| Treatment                                               | HBV-active agents (<2/2)                                                                                                                                                                                                                                    | Binary                                                                                 |
| Liver fibrosis                                          | Fibroscan stage (1/2/3/4)
Fibroscan score ( $\leq$ F2, >F2)                                                                                                                                                                                              | Categorical
Binary                                                                  |

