Correlations within and between endpoints at each visit and change from baseline visit will be explored (e.g., correlation sCD14 and Fibroscan score at month 12) and between consecutive follow-up visits and change from baseline visit separately (e.g., correlation sCD14 at month 12 with Fibroscan score at month 24). The Spearman correlation, exploring the degree to which the relationship between two outcomes is monotonic, will be used between two continuous outcomes and between an ordinal and continuous outcome, and point-biserial correlation between a binary and continuous outcome.

The following univariate models will be fitted to estimate the association between with the known risk factors (covariates) listed in Table 2 with each endpoint separately, both univariable (one covariate - unadjusted) and multivariable (more than one covariate - adjusted):

1. Univariate logistic regression model with the binary outcome of liver disease progression during the study (yes/no) adjusted for CD4+ T-cells at study entry (except for variables related to CD4).
2. Univariate mixed regression model with each outcome the repeated continuous outcome in microbial translocation/immune activation, hepatic inflammation, and Fibroscan score (kPa) adjusted for CD4+ T-cells at study entry (except for variables related to CD4).

In model 2 the functional form of time in the model will be explored (i.e., linear or curvilinear [e.g., quadratic, cubic]), a random intercept will be included in these models to represent a random effect for subject and the structure of the residual (within-patient) variance-covariance matrix will explored (e.g., unstructured, AR(1),...).

We will examine longitudinal liver stiffness measured by Fibroscan as a continuous variable in kPa and compare between those classified as progressors and non-progressors via univariate mixed regression.

### 7.1.2 Aim 2

Longitudinal plots by subgroup will be created of the microbial translocation/immune activation outcomes, hepatic inflammation outcomes, and liver disease outcomes. We will start by exploring subgroups in the univariate models outlined in Aim 1 by including appropriate interaction terms. It should be noted that the sample size will be a limiting factor in detecting statistically significant subgroup differences.

Analyses will be conducted using STATA, SPSS, or SAS.

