## Appendix 1 - Schedule of assessments

| Assessment                              | Baseline visit (0) | Follow-up visits |              |              |              |              |              |
|-----------------------------------------|--------------------|------------------|--------------|--------------|--------------|--------------|--------------|
|                                         |                    | 1 (Month 6)      | 2 (Month 12) | 3 (Month 18) | 4 (Month 24) | 5 (Month 30) | 6 (Month 36) |
| Informed consent                        | X                  |                  |              |              |              |              |              |
| History                                 | X                  |                  |              |              |              |              |              |
| Clinical examination                    | X                  | X                | X            | X            | X            | X            | X            |
| Concurrent medications & conditions     | X                  | X                | X            | X            | X            | X            | X            |
| Adherence & alcohol questionnaires      | X                  | X                | X            | X            | X            | X            | X            |
| Full Blood Count (FBC)                  | X                  | X                | X            | X            | X            | X            | X            |
| Biochemistry and liver function profile | X                  | X                | X            | X            | X            | X            | X            |
| HIV RNA level                           | X                  | X                | X            | X            | X            | X            | X            |
| CD4/CD8                                 | X                  | X                | X            | X            | X            | X            | X            |
| Hepatitis serology:                     |                    |                  |              |              |              |              |              |
| HBsAg                                   | X                  | X                | X            | X            | X            | X            | X            |
| Anti-HBs                                | X                  | X                | X            | X            | X            | X            | X            |

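### ALT, AST and albumin are measured at seven visits but modelled at four, so their trend models are less precise than the collected data allow

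*SAP*

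**What the plan says.** SAP Section 1 describes follow-up "with study visits every 6 months (baseline, 6, 12, 18, 24, 30, and 36 months of follow-up". Of liver stiffness and cells it says: "Liver fibrosis (assessed by transient elastography) and peripheral blood mononuclear cells (PBMCs) were assessed at baseline then annually".

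Table 2 (Section 5) gives the row holding ALT, AST and albumin the label "Hepatic Inflammation Collected 6-monthly (7) analysed yearly (4". The rows for plasma markers carry the same rule. In Appendix 1 the line "Biochemistry and liver function profile" is marked at baseline and at each of the six follow-up visits.

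These three markers enter model 2 of Section 7.1.1: "Univariate mixed regression model with each outcome the repeated continuous outcome", with hepatic inflammation among the listed outcome groups. On the covariance, "a random intercept will be included in these models to represent a random effect for subject", while the within-patient residual structure is left open: "variance-covariance matrix will explored (e.g., unstructured, AR(1". The form of time may be linear, quadratic or cubic. Aim 2 adds subgroup interactions to the same models. The SAP gives no reason for the yearly restriction.

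**The concern.** A yearly grid is natural for Fibroscan, which was done only yearly, and for stored-plasma markers, where each further visit needs another assay. Neither reason applies to ALT, AST and albumin, which are scheduled as routine tests at every visit. Model 2 treats each outcome separately and does not use the concurrent Fibroscan value, so it needs no common grid. Only the correlations between outcomes need matched visits.

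At stake is the precision of the time trends in the three markers and of subgroup differences in those trends. The SAP itself says in Section 7.1.2 that sample size limits what subgroup comparisons can show.

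**Working it through.** **Inputs from the SAP.** Follow-up is 36 months, with visits every 6 months (Section 1) and yearly analysis (Table 2). "The analysis set consists of all 67 participants across all sites" (Section 4). Within-person correlation (ICC), serial correlation and slope variation are not given, so they are assumed over ranges. All scheduled visits are taken as attended.

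**Visit counts.** 36/6 + 1 = 7 and 36/12 + 1 = 4, which reproduces Table 2. Planned values per marker are 67 × 7 = 469 and 67 × 4 = 268. The difference of 201 (43%) stays out of the yearly analyses.

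**Slope, random intercept and independent residuals.** The slope variance is proportional to 1/Sxx, where Sxx = Σ(t − 1.5)² in years².
- Four visits (0, 1, 2, 3): 2.25 + 0.25 + 0.25 + 2.25 = 5.0.
- Seven visits (0, 0.5, …, 3): 2 × (2.25 + 1.00 + 0.25) + 0 = 7.0.
- Variance ratio, seven to four: 5/7 = 0.714, a 29% cut at any ICC. The four-visit standard error is √(7/5) = 1.183 times the seven-visit one.

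**Slope, with true slope variation between people.** If a share r of the four-visit variance of individual slopes is true variation, the ratio is r + (1 − r) × 5/7. For r = 0.2, 0.4 and 0.6 (assumed) this is 0.771, 0.829 and 0.886, so cuts of 23%, 17% and 11%.

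**Slope, random intercept plus pure AR(1) residuals.** The variance is the slope element of (X′V⁻¹X)⁻¹, with V = τ²J + σ²R and R having entries ρ^|t−s|. Here ρ is the one-year correlation (assumed).

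| ρ | Variance ratio, 7 to 4 visits | Cut | Four-visit SE larger by |
|---|---|---|---|
| 0.1 | 0.916 | 8.4% | 4.5% |
| 0.3 | 0.981 | 1.9% | 1.0% |
| 0.5 | 0.996 | 0.4% | 0.2% |

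Pure AR(1) allows no independent visit-to-visit noise. If such noise has the same variance as the AR(1) part (assumed), the ratios at these ρ are 0.825, 0.871 and 0.879, so cuts of 18%, 13% and 12%.

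**Mean-level covariate effects, independent residuals.** The ratio is (ICC + (1 − ICC)/7) / (ICC + (1 − ICC)/4).
- ICC 0.5: 0.5714/0.6250 = 0.914, a cut of 9%.
- ICC 0.7: 0.7429/0.7750 = 0.959, a cut of 4%.

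**Form of time.** A cubic has four mean parameters. On four occasions it leaves 4 − 4 = 0 degrees of freedom to check the mean curve; on seven it leaves 7 − 4 = 3.

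**The case against.** The strongest reply is that this is an openly stated choice, not an error. The yearly rule applies to every Table 2 row that separates collection from analysis frequency. It matches the Fibroscan grid, and Aim 1 relates markers to a liver outcome measured yearly. That stands as far as it goes: nothing is contradictory, and no estimate is biased. It does not explain why model 2, which needs no alignment, should use fewer values than were collected.

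The reply is also right that the gain may be small. AR(1) is one of the structures the SAP names, and under pure AR(1) the gain nearly vanishes at moderate correlation. Model 2 is also framed around study-entry covariates, for which the mean-level gain is modest. An unstructured matrix has 4 × 5/2 = 10 parameters at four visits but 7 × 8/2 = 28 at seven, which is heavy for 67 participants.

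Some stronger inferences are tempting, and the SAP does not support them:
- **An equivalent sample size.** A reader might turn 7/5 into 67 × 7/5 = 94 participants. That holds only with no slope variation, no serial correlation and no dropout. Table 1 shows 58 of 67 followed to three years.
- **Harm to the missing-at-random analysis.** Values before dropout could matter, but at most 67 − 58 = 9 participants lack three-year follow-up. How many of them have an unused mid-year value is not stated.
- **The same fault for CD4 and CD8.** Their Table 2 row states no yearly limit, and model 2 does not name them as outcomes.
- **Data thrown away altogether.** Section 7.1.1 plans summaries at each follow-up time point, and output 2C in Section 11 covers liver function over time with no yearly label. The omission is shown only for the analyses that Table 2 labels yearly.

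**Conclusion.** The point holds as an avoidable and unexplained loss of efficiency in the ALT, AST and albumin models. Four visits are never more precise than seven in any structure examined, but the size of the loss depends on a residual structure that the SAP leaves open. The 29% slope-variance figure is an upper limit among those structures, not an expected value. The gain for mean-level effects is small throughout.

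The point does not reach the main liver results. The logistic models of progression, the Fibroscan model in kPa and the Aim 2 question on fibrosis progression rest on Fibroscan, measured four times, and gain nothing. All figures assume complete attendance. Those other than the visit counts and the independent-residual slope ratio also rest on assumed correlations or variance shares.

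**What to change.** In Table 2, change the hepatic inflammation row so that the values collected at seven visits are analysed at all seven in model 2, with the four yearly values kept for correlations with Fibroscan. Leave the stored-plasma markers yearly. If the yearly grid is kept for ALT, AST and albumin, state the reason. Also say which visits the descriptive summaries of these markers cover.

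Prefer a parsimonious residual structure that suits 6-monthly spacing over an unstructured matrix with 28 parameters.

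The cost is a wording change, a longer input data set and some re-running, since Section 13 reports that adjusted models have already been fitted. No new samples or assays are needed.
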